## Abstract

**Background/Objectives**: Anxiety disorders (ADs) affect up to 20% of mothers in the postpartum period, characterized by psychological symptoms (e.g., emotion dysregulation; ER) and physical symptoms (e.g., disrupted bodily awareness). Although Cognitive Behavioural Therapy effectively reduces anxiety and mood symptoms, it shows limited efficacy in addressing ER difficulties and rarely targets interoceptive dysfunction—both common in postpartum ADs. This study evaluates the effectiveness of a brief mindfulness-based intervention in improving anxiety, ER, and interoception in mothers with postpartum ADs. A secondary aim is to examine changes in brain connectivity associated with these domains. **Methods**: This protocol describes a proof-of-concept randomized controlled trial involving 50 postpartum mothers with ADs. Participants will be randomized to receive either a 4-week mindfulness intervention plus treatment-as-usual (TAU) or TAU alone. Participants in the mindfulness + TAU group will complete a virtual 4-week group intervention adapted from Mindfulness-Based Cognitive Therapy. The TAU group will receive usual care for 4 weeks and then be offered the mindfulness intervention. Self-report measures of anxiety, ER, and interoception will be collected at baseline, post-intervention, and at a 3-month follow-up. Resting-state functional MRI will be conducted at baseline and post-intervention to assess functional connectivity changes. This trial has been registered on ClinicalTrials.gov (NCT07262801). **Results:** Improvements in anxiety, ER, and interoception are anticipated, along with decreased default mode network, and increased salience network connectivity post-intervention is hypothesized. **Conclusions**: This study will be the first to examine the combined psychological and neural effects of mindfulness in postpartum ADs, offering a potentially scalable mind–body treatment.

## 1. Introduction

### 1.1. Impact of Postpartum Anxiety Disorders

Anxiety disorders (ADs) affect approximately one in five mothers and birthing parents (hereafter referred to as “mothers/BPs”) during the postpartum period (birth up to one year following delivery) [1,2]. These disorders are associated with significant distress and impair a mother/BP’s ability to care for themselves and their infant [3] and have been linked to lower parenting competence [4], lower marital satisfaction [5], and a higher risk of substance use and suicide [6]. Mothers/BPs with ADs are also less likely to breastfeed [7] and more likely to experience difficulties in responsiveness and bonding [8]. These disruptions are associated with adverse child outcomes, including challenges with temperament (e.g., less easily soothed), emotion regulation (e.g., developing anxiety disorders), and behavioural problems in early childhood [9,10,11,12,13]. Despite the significant prevalence and impact of ADs during the postpartum period, their underlying mechanisms remain unclear, and effective nonpharmacological treatments that are scalable and durable are limited.

### 1.2. Emotion Dysregulation and Interoception: Emerging Targets

Increasing evidence points to emotion dysregulation as a critical underlying process in ADs, including those that occur during the postpartum period. Perinatal changes to the endocrine and hypothalamic–pituitary–adrenal (HPA) axis heighten vulnerability to emotional instability [14], and even in the absence of clinical levels of anxiety, perinatal individuals show greater emotional reactivity and mood fluctuations [15,16,17,18]. Maternal emotion dysregulation, in turn, has been linked to reduced supportive parenting, as well as infant emotion dysregulation and later adjustment problems [19,20,21]. Among those with clinical levels of postpartum anxiety and/or depression, lower positive affect, higher negative affect, and reduced emotional flexibility have been observed compared to healthy perinatal individuals [22]. Yet despite the clear link between emotion dysregulation and postpartum anxiety, emotion regulation is rarely addressed as a direct target in psychological interventions for ADs during the postpartum period.

Anxiety symptoms have also been linked to disrupted interoception—the ability to sense, interpret, and regulate internal bodily signals [23]. Most existing research has focused on cardiac interoception in non-perinatal populations, with no studies to date examining postpartum mothers/BPs with ADs [24]. For example, individuals with generalized anxiety disorder have shown altered heartbeat-evoked potentials, suggesting impaired cortical processing of interoceptive signals [25]. A recent meta-analysis also found that anxiety was associated with negative interpretations of bodily sensations, hypersensitivity to internal cues, and difficulty articulating emotional or physical states [26]. These findings position disrupted interoception as a potentially important yet understudied mechanism in postpartum anxiety, one that, like emotion regulation, may be valuable to target in future interventions.

### 1.3. Current Treatments for Postpartum Anxiety Disorders

Practice guidelines in Canada [27,28], the UK [29], and the USA [30] recommend non-pharmacological approaches as first-line treatments for perinatal anxiety. Cognitive behavioural therapy (CBT) is the most widely supported psychological treatment for ADs [31], though its effects on core mechanisms like emotion regulation and interoception remain underexplored. Existing evidence suggests that emotion dysregulation reduces CBT’s effectiveness in several anxiety populations [32,33], yet only one study has examined this in perinatal individuals. Agako et al. [34] found that mothers with high pre-treatment emotion dysregulation remained dysregulated post cognitive behavioural group therapy, suggesting a need for more targeted interventions. Similarly, although disrupted interoception is increasingly recognized as central to the development and maintenance of anxiety [24], its role in the treatment of ADs during the postpartum period has not been studied.

### 1.4. Mindfulness-Based Interventions

In light of the limitations of existing psychological interventions—namely, their lack of explicit focus on emotion dysregulation and disrupted interoception as core components of anxiety—mindfulness-based interventions (MBIs) have emerged as a compelling alternative. Mindfulness teaches individuals how to improve their relationship with their thoughts, emotions, and bodily sensations, addressing both psychological and physical symptoms [35,36]. MBIs show moderate effectiveness in reducing anxiety and improving mood in both clinical [37,38,39,40] and non-clinical populations [41,42,43], with emerging evidence suggesting that they are also associated with neurobiological changes in brain networks supporting emotion regulation (e.g., the salience network; SN) [44], self-awareness (the default mode network; DMN) [45], and executive function (the central executive network; CEN) [46].

The current literature on MBIs in perinatal populations has predominantly focused on pregnancy, where consistent improvements in anxiety and depressive symptoms have been reported (medium–large effect sizes) [47,48,49,50,51,52]. In contrast, postpartum studies are limited and often include mixed clinical and subclinical anxiety samples [53,54,55]. Critically, no study to date has targeted postpartum individuals with diagnosed ADs or examined associated neurobiological outcomes, highlighting a key gap and opportunity for intervention.

### 1.5. Current Study

Given the physical and psychological components of ADs and the promising effects of mindfulness intervention on anxiety, emotion regulation, and interoception in non-postpartum populations, we developed a mindfulness protocol for postpartum mothers/BPs with ADs. This proof-of-concept randomized controlled trial will examine the effects of a 4-week mindfulness-based group intervention compared to treatment as usual (TAU). The primary aim is to evaluate the intervention’s impact on AD symptoms using both subjective (self-reported anxiety, emotion regulation, and interoception) and objective (functional connectivity of brain networks associated with these processes) measures. We hypothesize that participants will show reductions in anxiety and improvements in emotion regulation and interoception. We also expect to observe changes in functional connectivity in relevant brain networks (e.g., the DMN and SN). To our knowledge, this will be the first study to assess the efficacy of a mindfulness protocol for postpartum mothers/BPs with ADs using a combination of self-report and neuroimaging outcomes.

## 2. Materials and Methods

### 2.1. Inclusion/Exclusion Criteria

Participants will be included in this trial if they meet the following criteria: (1) Mothers/BPs 18 years and older who are between 0 and 12 months postpartum; (2) principal diagnosis of an AD as per the Diagnostic Assessment Research Tool (DART) [56,57], with or without comorbid mood disorder; (3) no concurrent psychological treatment; (4) not taking psychoactive medication or (a) medications are stable in dose and type for at least 8 weeks prior to the study and (b) medications remain stable throughout the study; (5) fluent in English, minimal grade 8 reading level. Exclusion criteria are as follows: (1) Severe depression/suicidality requiring acute intervention; (2) presence of current psychotic symptoms or alcohol or substance use disorders; (3) suffering from claustrophobia; (4) metallic objects in the body (e.g., metal implants, pacemakers) or any other contraindication for brain MRI procedures (e.g., currently pregnant).

### 2.2. Sample Size

In keeping with the minimum of 30 participants required to estimate a parameter in pilot and proof-of-concept trials [58,59], and based on prior studies applying neuroimaging to evaluate the impact of a mindfulness-based group intervention in non-perinatal anxiety and mood populations [37,38,60,61,62,63,64], a minimum of 20 participants will be randomized to each arm. Accounting for an estimated 20% attrition, we will recruit 50 participants total (25 per arm).

### 2.3. Study Design and Procedure

This study is an investigator-initiated, single-centre, proof-of-concept randomized controlled trial. The study will be conducted within the Women’s Health Concerns Clinic (WHCC) and the Imaging Research Center (IRC), St. Joseph’s Healthcare Hamilton, Canada. As part of standard care within the WHCC, clinicians who believe a patient may benefit from psychological treatment for postpartum anxiety and who have agreed to be contacted for research (i.e., individuals who agreed to complete self-report demographic and clinical questionnaires as part of the Green Prospective Database; HiREB # 1052) may refer them to a group-based intervention. If they meet eligibility criteria based on their routine pre-treatment diagnostic assessment, a study staff member will contact them to confirm interest and finalize study eligibility (Figure 1).

Eligible participants will be contacted via telephone following their routine care diagnostic assessment by study staff to gauge interest in participation in the present pilot randomized controlled trial. If interested, participants will be sent a password-protected information and consent form via e-mail while on the phone with study staff. During the phone call, study staff will review the consent form with the participant, providing the opportunity to ask questions and clarify the risks and rules associated with Zoom. Following the informed consent process, participants will be asked to sign a copy of the consent form, using a digital signature, while on the phone with study staff, to ensure that it is the participant signing the form. Once signed, the participant will email the signed consent form back to the study staff, the study staff will add their digital signature to the consent form, and will return a copy of the signed consent form to the participant via email.

Eligible and consenting participants will be randomly assigned to either the experimental (4-week mindfulness-based group intervention) or the TAU control group. Participants will be randomized using block randomization, with a 1:1 allocation ratio, using a computer-generated assignment sequence prepared prior to the study. Participants randomized to the mindfulness-based intervention group will complete a battery of self-report questionnaires post-treatment (Time 2) and 3 months post-treatment (Time 3). Questionnaires completed at Time 2 and Time 3 will be the same as those completed at baseline (Time 1) as part of the Green Prospective Database. Participants randomized to the TAU control group will complete the same battery of self-report questionnaires at Time 2. All questionnaires will be completed via Research Electronic Data Capture (REDCap). Participants randomized to the experimental group will also participate in an imaging session at the IRC at Time 1 and Time 2.

Participants randomized to the mindfulness-based intervention group will receive a $20 e-gift card for completing baseline questionnaires, post-treatment questionnaires, and another $20 after completing the 3-month follow-up questionnaires. They will also receive a $30 e-gift for participating in fMRI scans at baseline and post-treatment (for a total maximum of $120). Participants randomized to the TAU control group will receive a $20 e-gift card for completing baseline questionnaires and $20 after completing questionnaires following the 4-week TAU period (for a total maximum compensation of $40).

In addition to receiving financial compensation and the intervention being delivered entirely online, other attrition mitigation strategies have been put in place. Study staff will maintain regular contact via email and phone to remind participants about sessions and questionnaire-completion. Informal childcare support will be provided during MRI appointments, where a trained research assistant will be present while the participant completes the scan.

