### 2.5. Study Arms

The 4-week mindfulness-based group intervention involves participating in a 4-week group that meets once a week, for 2 h. The session will be delivered through Zoom. Sessions will be delivered by a senior-level Ph.D. student in clinical psychology (ZB) and a clinical psychologist ([name], CP). Each session will consist of psychoeducation about anxiety during the perinatal period and mindfulness practices designed to foster a state of mindfulness and improve anxiety symptoms. To encourage daily practice, links to guided meditation (i.e., SoundCloud links) will be included in the mindfulness protocol shared with participants. The intervention protocol was adapted from existing evidence-based protocols, including the Mindfulness-based Cognitive Therapy for depression protocol [65], as well as other perinatal-specific protocols [25,50,52,55]. The content provided in each session is detailed in Table 1.

Intervention fidelity will be monitored using a session-level adherence checklist. A trained research assistant will be present for the full duration of each group session and will complete the checklist following each session to document adherence to core intervention components (e.g., psychoeducation content, mindfulness practices, and session structure). These procedures are intended to ensure the consistency of intervention delivery across sessions and groups.

The minimum attendance requirement is attending 3/4 sessions to be included in the primary analysis. In instances where a participant cannot attend a session, an individual make-up session will be delivered by one of the group facilitators. In addition to tracking attendance, recording of any technical disruptions related to virtual delivery will also be recorded.

Participants in the TAU control group will engage in TAU for 4 weeks (waitlist period), which entails continuing to meet with their healthcare practitioners on an as-needed basis. This includes meeting with their psychiatry team, attending regular evaluations within the hospital, and/or meeting with other allied health professionals such as social workers, nurses, or counsellors. The one restriction that is placed on the 4-week waitlist period is not engaging in any formal, structured psychotherapy (e.g., CB, DBT, or other mindfulness-based interventions). After the 4-week TAU period, participants will be given the option to complete the 4-week mindfulness intervention.

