### 2.7. Participation Time Commitment

Total participation time for the experimental group is approximately 13–15 h across the 4-week intervention and follow-up period. This includes four 2 h virtual group sessions (8 h), completion of self-report questionnaires at three time points (piloting indicated that Time 1 requires approximately 15–20 min, as many measures are already part of the GPD [see page 5], and Time 2 and Time 3 each require less than 30 min; ~1–1.5 h total), two MRI sessions of approximately 20 min each (approximately 1 h including preparation), and strongly encouraged home mindfulness practice (recommended 10–20 min per day, flexible in timing). Participants in the TAU group complete approximately 1–1.5 h of questionnaire-related activities across two time points. As indicated, the participants will be compensated for all questionnaire and scan completions. Compensation is structured to acknowledge time and inconvenience rather than to function as an inducement. The compensation rates are consistent with those used in local perinatal mental health and neuroimaging research, including those in our research group, and were approved by the institutional Research Ethics Board.

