### 2.12. Data Analysis

To determine condition differences on the self-report clinical outcomes, a series of repeated measures analysis of variance (ANOVAs) will be used. A two (experimental group vs. TAU group) by two (Time 1 vs. Time 2) repeated measures ANOVA will be used to examine differences. Further, in order to determine if benefits are maintained long-term, a within-subject repeated measures ANOVA will be conducted for the experimental group across three testing times (Time 1, Time 2, Time 2). The primary outcome (STICSA) will be evaluated at α = 0.05. All other self-report measures are secondary, pre-specified a priori, and Bonferroni correction will be applied to account for multiple comparisons where appropriate. Given the proof-of-concept nature of the study, findings from secondary outcomes will be interpreted cautiously. Partial eta-squared (η^2^) will be reported for ANOVA effects, and Cohen’s d with 95% confidence intervals will be calculated to inform future sample size calculations. Analyses will follow an intent-to-treat (ITT) approach, with missing data handled using appropriate methods (e.g., multiple imputation where assumptions are met). All analyses will be performed with IBM SPSS Statistics 23 [93].

Preprocessing of fMRI data will be conducted using a combination of SPM12 (http://www.fil.ion.ucl.ac.uk/spm/software/spm12; accessed on 22 November 2025), FSL (https://fsl.fmrib.ox.ac.uk/fsl/fslwiki/; accessed on 22 November 2025), and custom MATLAB (version R2025b) scripts. Preprocessing will include motion correction, coregistration to the structural image, spatial normalization, nuisance regression (motion parameters and white matter/cerebrospinal fluid signals), and temporal band-pass filtering. ROI-to-ROI functional connectivity analysis will be performed using SPM to evaluate changes in connectivity within the DMN and SN. A priori-defined regions of interest (ROIs) for the DMN include the medial prefrontal cortex and posterior cingulate cortex, and for the SN include the anterior insula and dorsal anterior cingulate cortex. Growth curve analyses will be conducted within a linear mixed-effects modelling framework to assess changes in resting-state functional connectivity over time. A linear mixed-effects model will be used to examine both within-subject changes over time (Time 1 vs. Time 2) and between-group differences (experimental group vs. CAN-BIND healthy controls).

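### Three-month scores collected only in the mindfulness arm describe its course after treatment; they cannot determine whether benefits are maintained

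*Protocol article*

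**What the plan says.** Section 2.3 (Study Design and Procedure) schedules the mindfulness arm for questionnaires at baseline, after treatment (Time 2) and three months later (Time 3). For the other arm it says "Participants randomized to the TAU control group will complete the same battery of self-report questionnaires at Time 2". Section 2.7 (Participation Time Commitment) agrees: "Participants in the TAU group complete approximately 1–1.5 h of questionnaire-related activities across two time points".

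Section 2.5 (Study Arms) adds "After the 4-week TAU period, participants will be given the option to complete the 4-week mindfulness intervention". No assessment during or after that delayed course is described.

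Section 2.12 (Data Analysis) confines the between-arm analysis to the first two time points: "A two (experimental group vs. TAU group) by two (Time 1 vs. Time 2) repeated measures ANOVA will be used to examine differences". For the longer term it says "in order to determine if benefits are maintained long-term, a within-subject repeated measures ANOVA will be conducted for the experimental group".

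The abstract reports the schedule without naming an arm: "Self-report measures of anxiety, ER, and interoception will be collected at baseline, post-intervention, and at a 3-month follow-up".

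**The concern.** A benefit is a difference from what would have happened without the intervention. The randomised contrast that supplies this difference ends at Time 2. From then on there is one arm and no comparator, yet 2.12 states its purpose as determining whether benefits last.

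A good Time 3 score in the mindfulness arm has several possible sources besides a lasting effect:

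- natural improvement as the postpartum year passes;
- regression to the mean after entry on a diagnosis, which acts mainly on change from baseline;
- psychotherapy started after Time 2.

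On the last of these, section 2.1 requires medication to stay stable throughout the study, so medication change is at least addressed. Its rule on concurrent psychological treatment is an inclusion criterion, and nothing extends it to the three months after the course.

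No choice of test on the mindfulness arm alone can separate these sources. At stake is the three-month conclusion, which could be carried into the larger trial that the Discussion anticipates.

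**Working it through.** **1. Who is measured, and when.** The payments in 2.3 allow a check.

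- Mindfulness arm: 3 questionnaire rounds × $20 + 2 scans × $30 = $120, the stated maximum.
- TAU arm: 2 rounds × $20 = $40, the stated maximum.

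The assessment schedule in 2.3, the time commitment in 2.7 and the payments all give three rounds against two. The sample size also reproduces: 20 / (1 − 0.20) = 25 per arm, 50 in total, so about 20 completers per arm are expected.

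**2. What maintenance requires.** Count improvement as positive, in baseline SD. Let B2 and B3 be the benefit at Time 2 and Time 3, M the mindfulness arm's change from Time 2 to Time 3, and N the change that untreated mothers would have shown over the same period. Then

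B3 = B2 + M − N.

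The trial estimates B2 (randomised) and M (observed). It has no information on N.

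**3. Size if the benefit is wholly lost.** Assume B2 = 0.5 and B3 = 0, so M = N − 0.5. N is an assumption, because the documents give no figure.

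| Assumed N (SD) | Observed change M (SD) | How it would read |
|---|---|---|
| 0.2 | −0.3 | 60% of the benefit visibly lost |
| 0.5 | 0 | full maintenance |

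**4. Size if there was never any effect.** Assume zero treatment effect, natural improvement g between Time 1 and Time 3 (linear in time), within-person correlation r of 0.5 to 0.7, two-sided α = 0.05 and n = 20 completers. For the paired Time 1 to Time 3 test, the noncentrality is g√n / √(2(1 − r)). With g = 0.3 and r = 0.5 it is 0.3 × 4.472 / 1 = 1.34, and the test is significant in 24.7% of trials. The omnibus column is the three-time repeated measures F test under compound symmetry.

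| g (SD) | Time 1 vs Time 3 significant | Omnibus F significant |
|---|---|---|
| 0 | 5% | 5% |
| 0.2 | 14–20% | 12–16% |
| 0.3 | 25–38% | 21–32% |
| 0.5 | 57–78% | 50–74% |

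**5. What added TAU assessments would give.**

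- *Early versus delayed offer at Time 3.* With 20 per arm and no baseline adjustment, the 95% CI half-width is t(0.975, 38) × √(2/20) = 0.64 SD.
- *Pooled change from before to after the course.* With r = 0.6 assumed, the half-width is t(0.975, n − 1) × √(2(1 − 0.6)) / √n. This gives 0.42 SD for n = 20, 0.33 for n = 30 (half of 20 TAU completers take the course) and 0.29 for n = 40 (all do). The interval narrows, but the change is still uncontrolled.

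**The case against.** The strongest reply is that a missing untreated comparator at three months is the ordinary price of a waitlist design. Once TAU participants have been offered the course, measuring them at Time 3 does not bring an untreated group back. Section 2.12 openly calls the analysis within-subject and claims no between-arm effect at three months, the trial is labelled proof-of-concept, and the primary comparison is untouched. All of this stands. It limits the point to what may be concluded from Time 3 and makes extra TAU assessments an addition, not a cure. It does not rescue the stated purpose, because one arm cannot determine maintenance.

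A reader might be tempted further, in ways the documents do not support:

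- *That delayed-treatment data are discarded.* None are planned, so nothing collected is lost.
- *That the psychotherapy restriction in 2.5 lapses for the mindfulness arm after week 4.* That sentence governs the TAU waitlist period. The relevant text for both arms is in 2.1.
- *That a vanished benefit would generally look fully maintained.* In the illustration this happens only at the extreme assumption of 0.5 SD natural improvement.
- *That the abstract contradicts the methods.* It names no arm. It is incomplete in a way that could mislead, but it is not a contradiction.

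**Conclusion.** The point holds for the three-month aim only. Time 3 exists in one arm, so the planned ANOVA describes the course of symptoms after treatment and cannot tell a maintained effect from natural change, regression to the mean or later psychotherapy.

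The size depends on assumptions the documents cannot settle. With 0.2 to 0.5 SD natural improvement after Time 2, a wholly lost 0.5 SD benefit would show as a loss of 0.3 to 0 SD. With no effect at all and 0.2 to 0.5 SD natural improvement by Time 3, the uncontrolled Time 1 to Time 3 test would be significant in about 14% to 78% of trials with 20 completers. The randomised Time 1 to Time 2 comparison on the STICSA is unaffected, and offering the course to TAU participants is not at fault.

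**What to change.** **Wording, at no cost.** In 2.12, replace the maintenance aim with a statement such as: three-month scores are an uncontrolled within-group description of the mindfulness arm and do not separate a maintained effect from natural recovery or later treatment. In the abstract, say that the three-month follow-up is in the mindfulness arm only. In the same paragraph of 2.12, correct the list of three testing times, which prints Time 2 twice where Time 3 is evidently meant.

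**Cheap addition.** In 2.3, have the TAU arm complete the same REDCap battery at the same time from randomisation as the mindfulness arm's Time 3, whether or not they took the course, and also after the delayed course for those who take it. Record psychotherapy and medication changes since Time 2 in both arms. In 2.12, report Time 3 as randomised early versus delayed offer, with its confidence interval. Pooled change in TAU participants who opt in should stay descriptive.

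**Cost.** At the plan's $20 per round, 25 × $20 = $500 for one round and $1,000 for two, plus a protocol and consent amendment. Section 2.7 puts a Time 2 or Time 3 round at under 30 minutes, so the extra burden on the TAU arm is small. Because of crossover, the added comparison is not treated versus untreated, and with about 20 per arm it will be imprecise. If new data collection is declined, the rewording alone removes the overstatement.

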### 2.10. Exploratory Outcome

Resting-state Functional Connectivity: MRI data will be acquired using a 3T Discovery MR750 scanner (manufacturer: GE HealthCare; Chicago, IL, USA). Experimental group participants will undergo a 10 min anatomical MRI, followed by a 10 min resting-state fMRI during which they will be instructed to fixate on a cross. Changes in resting-state functional connectivity within the DMN and SN will be evaluated to examine whether improvements in self-reported anxiety, emotion regulation, and interoception are associated with neurobiological changes.

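### Only the mindfulness arm is scanned, so connectivity change has no randomised comparison, yet section 1.5 makes it a measure of the intervention's impact within the primary aim

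*Protocol article*

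**What the plan says.** **Who is scanned.** Section 2.3 of the protocol article: "Participants randomized to the experimental group will also participate in an imaging session at the IRC at Time 1 and Time 2". Section 2.10 agrees: "Experimental group participants will undergo a 10 min anatomical MRI, followed by a 10 min resting-state fMRI". For the TAU arm, section 2.3 provides only questionnaires: "Participants randomized to the TAU control group will complete the same battery of self-report questionnaires at Time 2".

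**What is compared.** Section 2.12 describes the imaging analysis this way: "Growth curve analyses will be conducted within a linear mixed-effects modelling framework to assess changes in resting-state functional connectivity over time". It then names a mixed model with two comparisons, Time 1 against Time 2 within subjects and the experimental group against CAN-BIND healthy controls. It mentions no comparison of mindfulness with TAU on connectivity.

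**What rank connectivity has.** There are three:
- Section 1.5, primary aim: "The primary aim is to evaluate the intervention’s impact on AD symptoms using both subjective" self-report and "objective (functional connectivity of brain networks associated with these processes) measures".
- Abstract, secondary aim: "A secondary aim is to examine changes in brain connectivity associated with these domains".
- Section 2.10, exploratory outcome, by its heading.

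**What caution is given.** Section 2.6 says that the CAN-BIND comparison uses historical data, is open to unmeasured differences, and is exploratory. No section says that the within-arm change is uncontrolled.

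**The concern.** An aim to evaluate an intervention's impact is causal. In this trial the causal evidence comes from randomising between mindfulness plus TAU and TAU alone, and only outcomes measured in both arms can draw on it. Connectivity is measured in one arm, so randomisation adds nothing to any connectivity estimate.

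Other parts of the text strengthen the causal reading. Section 1.5 closes by presenting the study as an assessment of efficacy that combines self-report with neuroimaging. The abstract's conclusion speaks of the neural as well as the psychological effects of mindfulness. Its methods describe two randomised arms and then scans before and after the intervention, without saying that only one arm has them. Someone who reads only the abstract would reasonably assume a controlled imaging result.

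At stake is what the trial may conclude. As section 1.5 is written, part of the primary aim cannot be answered by this design.

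**Working it through.** **1. Is only one arm scanned?** Payments and time commitment give an independent check.
- Experimental arm (section 2.3): three questionnaire payments of $20 and two scan payments of $30, so 3 × 20 + 2 × 30 = $120, the stated maximum.
- TAU arm (section 2.3): two questionnaire payments of $20, so 2 × 20 = $40, which matches "for a total maximum compensation of $40". Nothing is left for a scan.
- Section 2.7 counts MRI time for the experimental group and only questionnaire time for TAU.

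All sources agree.

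**2. How many are scanned?** Section 2.2 gives 20 per arm and 20% attrition: 20 / (1 − 0.20) = 25 per arm and 50 in total, which reproduces the plan's figure. The imaging contrast between arms is thus 25 randomised against 0 scanned in TAU.

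**3. What does the within-arm change estimate?** Let τ be the intervention effect on connectivity over the four weeks, and δ the change that would have occurred anyway (postpartum time, usual care, repeat scanning).
- Mindfulness arm: expected change = τ + δ.
- TAU arm: expected change = δ, but this is not measured.
- Randomised contrast: (τ + δ) − δ = τ, not available.

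One observed quantity has to carry two unknowns, and a larger sample does not help.

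**4. Does CAN-BIND supply δ?** It would have to show how anxious postpartum women under usual care change over the same interval. Its controls are healthy, historical and not randomised. The article does not say that they are postpartum or that they have a second scan over a matching interval. Even with repeat scans, they would not estimate δ for this population.

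**5. How much could this matter?** The documents give no drift size, so the following is an assumption shown over a range. Take τ = 0 and a paired t-test at two-sided 5%, with noncentrality = drift × √n and n − 1 degrees of freedom. The chance of a significant change is:

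| Drift (SD of change score) | n = 20 | n = 25 |
|---|---|---|
| 0 | 5% | 5% |
| 0.2 | 14% | 16% |
| 0.3 | 25% | 30% |
| 0.5 | 57% | 67% |
| 0.8 | 92% | 97% |

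A randomised between-arm test would stay at 5% throughout if drift were equal in both arms.

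**The case against.** The strongest reply is that the operative sections already treat imaging modestly. Section 2.10 is headed exploratory, section 2.6 cautions about CAN-BIND, the Discussion calls the salience-network analyses hypothesis-generating, and sections 2.8 and 2.12 make the STICSA the only primary outcome, tested at 0.05. Single-arm imaging is a legitimate choice in a 50-person proof-of-concept trial, and section 2.12 openly names CAN-BIND rather than TAU as the comparator. Much of this stands: section 2.10 needs no relabelling, and scanning one arm is not itself an error. What it does not answer is that section 1.5 and the abstract say something else, and that the section 2.6 caution covers only the CAN-BIND comparison.

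It is also fair to say that the drift values above are assumed. The documents give no evidence on the size of any drift, and regression to the mean is a weak candidate because eligibility rests on diagnosis, with no connectivity threshold.

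A reader might infer more than the documents support:
- **That a growth curve on two scans cannot be identified.** A random intercept, random slope, their covariance and a free residual would be four parameters against three observed second moments. But section 2.12 specifies no random slope, and with a random intercept the model is identified. The term is at most a loose label for a mixed model with two time points.
- **That the small number scanned is the defect.** With 20 to 25 pairs, the 95% interval for mean change has a half-width of about 0.47 to 0.41 SD of change (t/√n: 2.093/√20 and 2.064/√25). This describes precision, not the missing control.
- **That CAN-BIND must be restricted to a subgroup, or that a model for the symptom–connectivity association is missing.** The first is a preference. The second is detail that an article may leave to the analysis plan.

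**Conclusion.** The point holds as a mismatch between claim and design, and should be fixed. The trial has no randomised contrast for connectivity, so the intervention's share of any Time 1 to Time 2 change cannot be estimated, while section 1.5 and the abstract present connectivity as evidence of what mindfulness does. The three ranks given to the same measure are a contradiction within the document.

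That conclusion rests on the text alone and needs no numerical assumption. The table is illustrative: it depends on assumed drift, two-sided 5% testing and 20 or 25 complete pairs.

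A reader might also infer that the trial's main result is compromised. It is not: the STICSA is collected in both randomised arms at Time 1 and Time 2, and its comparison, alpha level and sample size do not depend on the imaging.

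**What to change.** 1. **Section 1.5:** remove connectivity from the primary aim and state it as an exploratory objective. Limit the closing efficacy statement to the self-report outcomes.
2. **Abstract:** change the rank from secondary to exploratory to match section 2.10, say that only the mindfulness arm is scanned, and reword the conclusion so that it does not promise neural effects of mindfulness.
3. **Sections 2.10 and 2.12:** state that Time 1 to Time 2 connectivity change is an uncontrolled single-arm description, reported as mean change with a 95% confidence interval, and that it cannot be attributed to mindfulness. Describing the model as a two-time-point mixed model would be clearer than calling it a growth curve.

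The cost is wording, plus giving up a causal imaging claim that the design could not support. Recruitment stays at 50 and no scans are added. Scanning TAU as well would create a randomised contrast, but is not needed for this fix. With 20 or 25 per arm, it would detect a difference in change of only about 0.91 or 0.81 SD (assuming 80% power, two-sided 5%).
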